# Effectiveness of LiuZiJue Qigong versus traditional core stability training for poststroke patients complicated with abnormal trunk postural control: study protocol for a single-center randomized controlled trial

**DOI:** 10.1186/s13063-020-4117-6

**Published:** 2020-03-12

**Keywords:** Six-character formula, Trunk postural control, Stroke, Core stability, Traditional core stability training, LiuZiJue Qigong (LQG)

## Abstract

**Background:**

Trunk function in stroke patients with hemiplegia is associated with respiration and core stability and is also found to be associated with balance and postural control and activities of daily living. LiuZiJue Qigong (LQG) is a traditional Chinese method of fitness based on breath pronunciation. The purpose of this study is to compare the clinical efficacy of LQG and traditional core stability training in the treatment of stroke patients with abnormal trunk posture. This protocol is written according to the SPIRIT 2013 statement.

**Methods/design:**

This study is a single-center randomized controlled trial in which 160 stroke patients are randomly divided into a study group and a control group. Patients in the study group will receive LQG combined with conventional rehabilitation therapy, and patients in the control group will receive traditional core stability training combined with conventional rehabilitation therapy. All treatments will be done for 45 min/day, five times per week, for 2 weeks. The primary outcome (Trunk Impairment Scale) and secondary outcomes (Berg Balance Scale, Fugl-Meyer Assessment, Modified Barthel Index, Maximum Phonation Time, Dynamic and Static balance testing, and thickness and the mobile degrees of diaphragm) will be measured at baseline, 2 weeks, and the end of the rehabilitation course.

**Discussion:**

The aim purpose of this research study is to compare the clinical efficacy of LQG and traditional core stability exercise in the treatment of stroke patients with abnormal trunk posture.

**Trial registration:**

Chinese Clinical Trial Register, ChiCTR1800014864. Registered on 24 November 2018.

## Background

Several studies have shown that trunk posture control disorder is common in patients with hemiplegia after stroke [1]. Therefore, the problem of trunk control disorder in stroke patients should receive more attention in the course of rehabilitation. It is characterized by trunk coordination and sitting balance problems, trunk posture control and trunk muscle strength, and trunk position perception [2]. “Postural control” refers to the ability to keep the body in appropriate space during all kinds of physical activities [3]. Correct postural control depends on valid core stability. The core muscle group is divided into the deep muscle and shallow movement muscle groups, in which the deep muscle group should play the main role in stabilizing the trunk [4]. The deep core muscles, such as the diaphragm, the abdominal transverse muscle, and the pelvic floor muscle, are also the main muscles responsible for breathing [5, 6]. For example, during inhaling, diaphragm centripetal contraction, diaphragmatic roof fall, abdominal and pelvic floor muscle centrifugal contraction, and increased intra-abdominal pressure occur, enhancing core stability. Obviously, deep core muscles are closely related to posture control and breathing ability [7, 8].

Currently, core stability training is often used as a clinical treatment for stroke. However, respiratory training is often neglected in the rehabilitation of stroke. To maintain the core stability of stroke patients with hemiplegia, the chest, pelvis, and abdominal cavity are in abnormal positions, and the breathing movements of the diaphragm are affected, resulting in overinvolvement of the auxiliary respiratory muscles, which exacerbates postural abnormalities. Therefore, it is very important to explore a treatment approach that combines respiration and trunk control to improve a stroke patient’s ability to control the trunk.

Inspiration is related to trunk extension, and exhalation is related to trunk flexion. Patients with hemiplegia often show abnormal chest uplift, collapsed abdominal muscle force on the hemiplegic side, and overextension of the trunk. Abnormal trunk posture control in poststroke patients could lead to abnormal breathing. Fugl-Meyer et al. found that decreased expiratory force is a common feature in stroke patients with hemiplegia [9]. In subsequent studies, it was also found that “abdominal electromyography decreased during forced exhalation” [10]. Patients with cerebral apoplexy generally have abnormal breathing, which is often manifested as decreased exhalation ability [11]. Because of all these factors, proper breathing exercises, especially exhalation exercises, are necessary in patients with stroke [12].

LiuZiJue Qigong (LQG) is a traditional fitness method that focuses on controlling breathing. It is part of a new fitness qigong series launched by the Chinese Health Qigong Association [13]. LQG involves performing the actions of inhaling and exhaling through different mouth patterns to regulate and control the rise and fall of the breath in the body, and completing the practice of “xu, he, hu, si, chui, xi” with breathing and pronunciation. These exercises significantly enhance the function of the liver, heart, spleen, lungs, kidneys, and trifocal organs, respectively, and LQG helps to balance the energy and function of the internal organs [14, 15]. The method includes breathing in through the nose and exhaling with enunciation of one of the six different voices and breathing sound [16].

Recent studies have shown that the six-character formula can effectively improve lung ventilation function in patients with chronic obstructive pulmonary disease (COPD) and improve their daily quality of life. It can enhance the cardiopulmonary function of patients with arrhythmia [15, 17]. Studies have shown that LQG improves symptoms, motor function, and daily quality of life in patients with Parkinson’s disease [18].

Abnormal breathing patterns are caused by abnormal trunk control. However, abnormal trunk control is related to muscle weakness of not only the hemiplegic side trunk but also the nonhemiplegic trunk. The six-character formula improves diaphragm function through one inhalation and six breaths, strengthens the control of the deep core stable muscle group, and increases the control ability of the bilateral trunk. Therefore, the aim of this research is to compare the clinical efficacy of LQG and traditional core stability exercise in the treatment of stroke patients with abnormal trunk posture.

## Methods/design

### Trial design

This study will be a single-center randomized controlled trial (RCT) in which 160 stroke patients will be randomly divided into study and control groups. The study will be conducted at Shanghai Xuhui Central Hospital between March 1, 2018, and March 31, 2021. The study will recruit eligible subjects from the inpatient and outpatient departments of rehabilitation medicine of Shanghai Xuhui District Central Hospital in Shanghai. Patients will be allocated in a 1:1 ratio to the study group or the control group. LQG combined with conventional rehabilitation will be completed by patients in the study group, whereas traditional core stability training combined with conventional rehabilitation will be completed by patients in the control group. The Trunk Impairment Scale (TIS) will be used as the main evaluation index. The secondary evaluations index will include the Fugl-Meyer Assessment (FMA), Maximum Phonation Time (MPT), Dynamic and Static Balance Testing (PK-254; TecnoBody, Dalmine, Italy), measurement of the thickness of the diaphragm, measurement of degrees of diaphragm mobility, Modified Barthel Index (MBI), and Berg Balance Scale (BBS). All assessments will be conducted at baseline, at 2 weeks, and at the end of the rehabilitation course. A flowchart of the study protocol is shown in Fig. 1. The research proposal has been designed according to the Standard Protocol Items: Recommendations for Interventional Trials (SPIRIT) 2013 statement recommendations (Fig. 2 and Additional file 1).

**Fig. 1 Fig1:**
[figure not shown]
Flowchart of the study

**Fig. 2 Fig2:**
[figure not shown]
Standard Protocol Items: Recommendations for Interventional Trials (SPIRIT) figure of the LiuZiJue Qigong study protocol

### Primary and secondary outcomes

In this study, the TIS will be the main observation index. At the same time, the clinical effect will be divided into three grades to evaluate the curative effect before and after treatment: complete response (CR), partial response (PR), and no response (NR). The results of this observation index will be defined as ranked data.

The secondary outcome measurements will include other relevant evaluation indicators, such as FMA, BBS, ADL, MPT, Dynamic and Static Balance Function, Diaphragm Thickness, and muscle mobility of the diaphragm. The data obtained from these indicators will be measurement data.

### Primary outcome measurement procedures

Experienced physicians will assess the primary measures before and after treatment for 2 weeks. The TIS will be used to measure the main results (Table 1).

**Table 1 Tab1:** Specific measurement of trunk posture control levels carried out by Trunk Impairment Scale

	Baseline	2 weeks
Trunk posture control measurement		
Evaluation date		
Signature of therapist		

A main investigator will evaluate trunk postural control in the entry and exit stages. Trunk postural control measurement will be conducted according to the Spanish version of TIS 2.0. This scale consists of three subscales. The subscale of the first item is “static sitting balance” (score range 0–7) to assess the ability of patients to maintain sitting balance by landing on their feet and crossing their legs. The patient should cross the leg on the affected side. The second subscale will evaluate dynamic sitting balance (score range 0–10) and assess the lateral flexion of the trunk, starting from the upper and lower trunk. The third subscale will evaluate coordination (score range 0–6) and test the ability to independently rotate the shoulder girdle and pelvic girdle. The total scores will range from 0 to 23, with a higher score denoting better performance [19].

We will evaluate efficacy before and after the intervention According to the following criteria:

CR: TIS total score increased ≥ 7 points after treatment

PR: 3 points ≤ TIS total score increased ≤ 6 points

NR: total TIS score after treatment ≤ 2 points or worse

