#### Sample size calculation

We will use the TIS as the main therapeutic index to evaluate trunk posture control. The preliminary experimental findings showed that the effective rate was 80% in the study group and 50% in the control group. The effective rates of the study group and the control group were set as 80% and 50%, respectively. On this basis, sample estimation was conducted using G*Power 3.1 software, and the rank-sum test was adopted to set the rates of 80% in the treatment group and 50% in the control group for bilateral testing, and we set α = 0.05 and power = 0.97 (the setting of this value is based on the statistical power after the end of the experiment; power = 0.97 after the end of 40 cases). The distribution ratio was matched by 1:1, and the final sample size was set as 142, with 71 subjects in each of the two groups, taking into account the possibility of 12% attrition rate during the study. Therefore, the total number of samples was finally determined to be 160 cases, namely 80 cases in each group.

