### Statistical analysis

In this study, the main indicators were determined according to the change levels of TIS before and after treatment, which were divided into three levels of CR, PR, and NR and expressed by rate or percentage. The chi-square test will be used to compare differences in efficacy between groups. The overall curative effect evaluation and the curative effect evaluation method will be employed. The calculation formula is as follows: Effective = (excellent + effective)/total cases × 100%. Secondary indicators (e.g., MPT, MBI, BBS, FMA, diaphragm thickness and mobility, static and dynamic balance ability) are all continuous data. A paired sample *t* test is often used for intragroup comparison, whereas an independent sample *t* test is often used for intergroup comparison of the difference between the two groups after treatment, and a two-sided test will be used with the significance level set at *P* ≤ 0.05. To eliminate the influence of rehabilitation intervention time, stroke type, age, and gender on the efficacy and relative size of intervention methods will be considered and the statistical method of stepwise logistic regression model adopted.

The intention-to-treat (ITT) group is divided into final analysis set (FAS) and per protocol (PP), where FAS refers to the data set obtained after minimal and fair removal of data from all randomized subjects. PP is sometimes referred to as “valid case” and “valid sample” and is a subset of the total analysis set. The subjects had sufficient adherence to the protocol to be able to estimate the effect of the treatment.

The PP population will include random patients in the ITT group but will exclude patients who do not meet the inclusion or exclusion criteria and randomly assigned patients who do not receive the actual treatment [33].

If the statistical results are the same, ITT and PP are reliable indicators. ITT results will be used if statistical evaluations are different between the two methods. As the final observation result (last observation carried forward), the missing data will be processed. The last observation value of the endpoint will be regarded as the follow-up evaluation point of missing data, and the last observation reaction will be regarded as the endpoint of the study.

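### The no-response grade of the primary endpoint is written on the post-treatment TIS total, not on the change, so patients who gain 0 to 2 points have no grade

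*Protocol article*

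**What the plan says.** All references are to the Protocol article.

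- **Primary outcome measurement procedures** gives three grades:
  - the top grade, set on the increase: "CR: TIS total score increased ≥ 7 points after treatment"
  - the middle grade, also set on the increase: "PR: 3 points ≤ TIS total score increased ≤ 6 points"
  - the bottom grade, set on the level reached: "NR: total TIS score after treatment ≤ 2 points or worse"
- The same section gives the scale's range and direction: "The total scores will range from 0 to 23, with a higher score denoting better performance".
- **Inclusion criteria** admits patients with a TIS of 6 to 17.
- **Primary and secondary outcomes** treats the three grades as ranked data.
- **Statistical analysis** puts the grades on the change: "the main indicators were determined according to the change levels of TIS before and after treatment, which were divided into three levels of CR, PR," with NR named as the third. On the test it says: "The chi-square test will be used to compare differences in efficacy between groups". It also defines a rate, as a percentage: "Effective = (excellent + effective)/total cases × 100".
- **Sample size calculation** states: "The effective rates of the study group and the control group were set as 80% and 50%, respectively".

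No section restates NR as a change in score.

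**The concern.** The first two grades measure how far a patient has moved, and the third measures where the patient has ended. The three lines therefore do not divide up one variable. A patient who goes from 10 to 12, or stays at 10, is too small a gainer for PR and far above the NR level.

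These grades are the primary endpoint. An endpoint rule should place every patient in exactly one category before outcomes are seen. Here the rule for the patients who do not respond has to be inferred at analysis, and at the planning rates they are unequally split between the arms.

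The missing-data rule feeds the same gap. Table 1 schedules the TIS at baseline and 2 weeks only, and missing values are filled by last observation carried forward. A patient without a 2-week score who is kept in the analysis has a change of 0, which has no grade.

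The rate formula adds a smaller difficulty: its two numerator labels are not among the three defined grades, so the reader has to map them to CR and PR.

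**Working it through.** **1. The plan's own sample size.** Inputs from Sample size calculation: rates 0.80 and 0.50, two-sided α = 0.05, power 0.97, 1:1 allocation. With pooled variance and no continuity correction:

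n per arm = [1.960 × √(2 × 0.65 × 0.35) + 1.881 × √(0.80 × 0.20 + 0.50 × 0.50)]² / 0.30² = (1.322 + 1.204)² / 0.09 ≈ 70.9, rounded up to 71.

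That is 142 in total, as stated. The calculation uses only the proportion with an effective result, so the NR wording does not enter it.

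**2. What the written NR rule requires.** The lowest entry score is 6, and 6 − 2 = 4, so a patient at the bottom of the range must lose at least 4 points. The highest is 17, and 17 − 2 = 15, so a patient at the top must lose at least 15.

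**3. Every possible pair of scores.** There are 12 baseline values (6 to 17) and 24 post-treatment values (0 to 23), so 12 × 24 = 288 pairs. These are counts of possible score pairs, not of expected patients.

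| Pairs | Count |
|---|---|
| CR (change of 7 or more) | 66 |
| PR (change of 3 to 6) | 48 |
| Change of 2 or less | 174 |
| – of these, post-treatment total of 2 or less (written NR) | 36 |
| – of these, no grade | 174 − 36 = 138 |

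No pair falls in two grades. For changes from −3 to +2, none of the 12 × 6 = 72 pairs meets the written NR rule.

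**4. The generous reading.** Suppose the closing words of the NR line mean any decline from baseline. Then all declines are NR, and the ungraded pairs are those with a change of 0, 1 or 2: 12 × 3 = 36. The gap is narrower but still there.

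**5. Patients at the planning rates.** Taking an effective result to mean CR or PR:

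- study arm: 0.20 × 80 = 16 neither CR nor PR
- control arm: 0.50 × 80 = 40 neither CR nor PR
- total: 56 of 160 = 35%

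The document does not say how many of these would deteriorate, so that share is an assumption. On the generous reading, the ungraded number is 56 if none declines, about 50 if 10% decline (56 × 0.90) and 42 if 25% decline (56 × 0.75). On the strict reading only falls to a total of 2 or less leave the ungraded group, so for any given share of decliners the number is at least as large.

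**6. What depends on NR and what does not.**

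- Effective rate over total cases: 64/80 = 80% and 40/80 = 50%. Unchanged, because ungraded patients are still cases.
- Three-grade table or ranked analysis: cannot be completed. If ungraded patients were left out, mainly CR against PR among 64 + 40 = 104 responders would remain, which is a different question.

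**7. After correction.** With NR defined as a change of 2 or less, all 288 pairs fall in exactly one grade (66 + 48 + 174 = 288), and the sample size stays at 142.

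**The case against.** The strongest reply is that the intended rule is plain. The Statistical analysis section places all three grades on the change. The cut-points (7 or more, 3 to 6, 2 or less) join up only as changes. With entry scores of 6 to 17, no analyst would take non-response to mean a final total of 2 or less. This stands as evidence of intent, and it makes the defect a wording error. It does not remove the error: the only operational definition of NR contradicts the analysis section.

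A second reply is that the chi-square test may be meant for the two-category effective rate. The text does not say which table it applies to, and 142 matches a two-proportion calculation. On that reading the NR line does no harm to the test. The three-level grading and its description as ranked data remain exposed, and the sample size section itself names a rank-sum test.

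Three stronger inferences are tempting but not supported:

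- *The effective rate goes to nearly 100% in both arms.* That needs ungraded patients to leave the denominator, and the formula divides by total cases.
- *The sample size is undermined.* It depends only on the effective rate and reproduces exactly.
- *Everyone who gains 2 points or fewer is ungraded.* Patients who fall to a total of 2 or less do meet the written rule, and on the generous reading so do all who decline.

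**Conclusion.** The point holds as an error in the wording of the primary endpoint. The NR line uses the post-treatment total where the other two grades, and the analysis section, use the change. Gains of 0, 1 or 2 points have no grade under either reading of the line. Falls that stop above a total of 2 have none under the strict reading.

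About 35% of the planned sample are neither CR nor PR, and most of them would be ungraded. This rests on the planning rates, on an effective result meaning CR or PR, and on few patients deteriorating. The damage is confined to the three-grade table and any ranked analysis. The intent is easy to infer, but the line should be corrected before outcome data are examined, so that handling of these patients is not a choice made after the fact.

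**What to change.** In Primary outcome measurement procedures, replace the NR line with:

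> NR: TIS total score increased by 2 points or less, unchanged, or decreased.

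In Statistical analysis, restate the formula in the defined grades:

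> Effective rate = (CR + PR) / total cases in the analysis set × 100%.

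The denominator refers to the analysis set because the article defines its analysis populations separately, and this correction need not reopen that choice.

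The cost is two sentences. Data collection, the CR and PR cut-points and the sample size do not change.

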### Secondary outcome measurement procedures

The secondary outcome measurements will include other relevant evaluation indicators, such as FMA, BBS, ADL, MPT, dynamic and static balance function, diaphragm thickness, and muscle mobility of the diaphragm (Table 2). Experienced physicians will evaluate the secondary outcomes at baseline and 2 weeks after treatment.

**Table 2 Tab2:** Comprehensive evaluation of trunk posture control disorders after stroke using Fugl-Meyer Assessment, Berg Balance Scale, activities of daily living, maximum phonation time, dynamic and static balance function, diaphragm thickness, and muscle mobility of the diaphragm

	Baseline	2 weeks
Fugl-Meyer Assessment		
Berg Balance Scale		
Barthel Index		
Static balance testing		
1. Displacement difference of the *x* and *y* axes		
2. SD of before and after, left and right directions		
3. Average motion speed before and after, left and right		
4. Motion length		
5. COP (central of pressure) area		
6. Area ratio and length ratio under the test of the motion area and Romberg		
Dynamic balance testing		
1. Trunk stability index (front and rear, left and right, circumference)		
2. Average trajectory error		
3. Test execution time		
4. Average weight force difference (kg)		
Maximum phonation time (s)		
Diaphragm thickness		
Muscle mobility of diaphragm		

*COP* central of pressure

The simplified FMA will be used for the assessment of motor function and is often used in clinical rehabilitation because it is reliable and effective [20, 21]. The scale has a total score of 100, which is divided into motor function evaluation of the upper and lower limbs, among which the upper limb score is 56 and the lower limb score is 44. Each item has a 3-point rating, and a higher score indicates better motor function. The classification of its dysfunction is as follows: < 50 = severe dyskinesia; 50–84 = significant dyspraxia; 85–95 = moderate dyskinesia; 96–99 = mild dyskinesia; and 100 = normal.

